### Behavioural intervention

#### Theoretical framework

This intervention was developed at the University of Birmingham by the study team and uses Self-Determination Theory (SDT) as a framework to help support behaviour change [22]. SDT is primarily a theory of motivation, and it posits that individuals have intrinsic desires to maximise achievement towards their long-term goals [23]. SDT is based on the premise that individuals have three fundamental needs: autonomy, competence, and relatedness, that must be satisfied for optimal motivation [24]. Consideration for supporting these basic psychological needs was used throughout the intervention design process (e.g. during selecting of behavioural change techniques (BCTs) and in specifying the intended consultation style) and the Basic Psychological Needs Scale was incorporated as an outcome measure to assess changes in these constructs over the course of the intervention [25, 26]. A sub-theory of SDT, called organismic integration theory, states that by supporting Basic Psychological Needs, extrinsically regulated behaviours (i.e. new “goals” revolving around sitting less and being more active) can move from a state of external regulation to integrated regulation [27]. In integrated regulation, these new behaviours align with the individual’s personal needs, and thus, the frequency of these behaviours will be maximised (Fig. 2).

**Fig. 2 Fig2:**
[figure not shown]
Logic model and integration of SDT into the INTEREST study’s design

#### Intervention materials

A sedentary behaviour booklet was developed and used in this intervention (see Additional file 1; Fig. 3). This booklet provides some brief education about the effect of sitting on health, walks participants through the process of making an action plan in collaboration with the researcher, provides space for them to write the plan, and offers space for recording goal adherence. Additionally, a Yamax SW200 Digi-Walker pedometer was provided to participants to allow them to track their daily step counts.

**Fig. 3 Fig3:**
[figure not shown]
Sedentary behaviour booklet developed for INTEREST

#### Intervention components

A previous review of studies incorporating interventions to reduce sedentary time in adults aged 18 years and older found that those which included more BCTs were more effective than those that involved fewer [28]. By reviewing the literature, we were also able to identify which behaviour change techniques were used in existing interventions in older adults, which was used to inform the present intervention [11]. The full rationale for these components is provided in Additional file 2.

The intervention is built upon the following main techniques:*Education:* Written information will be provided in a custom-designed “sedentary behaviour booklet” (Additional file 1) that summarises the latest research about sedentariness in older adults in a simple way. Verbal information will also be provided where appropriate during conversations with the participants.*Motivational interviewing*: The participant will take part in a motivational interviewing session of approximately 30 min during visit 2, designed to reduce ambivalence around the participant’s sitting and physical activity, to identify enablers, to break down barriers, and to explore and enhance the participant’s ability to change [29]. Motivational interviewing has been found to integrate well with SDT, as MI aims to support patient autonomy and the other basic psychological needs [30, 31]. These sessions will be delivered by a researcher trained in motivational interviewing (JA).*Individualised feedback:* In visit 1, participants will be given an accelerometer to wear for 3–7 days (activPAL, PAL Technologies, Glasgow, UK). Their summary baseline data will be shown to participants in the form of an easy to understand report generated by the bespoke software in visit 3. This will help inform the participant and the researcher about the participant's relative sedentariness and activity and to allow targeting of specific times of day with their goals.*Individualised, incremental goal setting*: In visit 3, participants will formulate six goals with the aid of the researcher, in a collaborative process that encourages them to generate their own ideas. These plans will be set using SMART criteria for each goal (i.e. specific, measurable, achievable, relevant, and timely). For example, participants might plan to “walk to the kitchen and back during every TV break” or “do five consecutive chair rises after every meal each day”. These goals are designed to reduce the length of sedentary bouts, reduce total sedentary time, and increase sit-to-stand transitions. Participants will be encouraged to add one goal per week, so in week 1, they are working on one goal, in week 3, they are working towards three goals, etc., up to 6 weeks and six goals. Goals will be recorded in the sedentary behaviour booklet.*Environmental modification:* Participants will make three modifications to their environments in a way that is supportive of a less sedentary lifestyle and will record these in the booklet. These could include something as simple as keeping the TV remote next to the TV so that they must get up to change the channel.*Self-monitoring:* Participants will be provided with a pedometer, with which they can track their step counts, and a space within the booklet where they can record their adherence to the action plan and document any problems they encountered.*Social support:* In some cases, it will be possible to incorporate spousal or familial support into the goals and environmental modifications made by the participants to help with adherence and encouragement. In addition to this, three biweekly phone calls with the researcher will use motivational interviewing techniques, where participants will be asked about progress on their goals and whether they have made any modifications to them, etc. This will aid the maintenance of participant motivation and adherence.

#### Intervention structure and delivery

Participants will receive up to five visits (Table 2). The usual care group will attend only three visits, namely, 1, 4, and 5, which are assessment-only visits. The intervention group, however, will also attend visits 2 and 3 (which may be combined if time permits). Visit 2 consists of the motivational interview, whereas visit 3 involves the goal-setting, environmental modification, scheduling of the phone calls, and provision of the pedometer. The intervention is designed to be non-burdensome to researcher and patient in order to make it realistically implementable in orthopaedic care, as the motivational interviewing, education, goal-setting, and environmental modification session can be delivered within a single 90–120-min session, with the addition of three 10-minute phone calls.

**Table 2 Tab2:** Standard Protocol Items Recommendations for Interventional Trials (SPIRIT) diagram to show the participant schedule, including enrolment, allocation, interventions, visits, and assessments [20]

	Study period										
	Recruitment	Baseline	Allocation	Post-allocation							Close-out
Visit	Pre-enrolment	Visit 1	Allocation between visit 1 and 2	Visit 2	Visit 3	PC 1	PC 2	PC 3	Visit 4	Visit 5	Post-study
Timepoint (weeks)	1	2	3	3	3	5	7	9	1 week prior to surgery	6 weeks post-surgery	
Study member	Research nurse	R	Third party	R	R	R	R	R	R	R	R
Enrolment											
Eligibility screening	X										
Informed Consent		X									
Allocation			X								
Study groups											
Sedentary behaviour reduction	X	X	X	X	X	X	X	X	X	X	
Regular care	X	X	X						X	X	
Assessments											
Feasibility (study statistics)											X
Feasibility (interviews with research nurses)											X
Feasibility (questionnaire, acceptability, practicality, adaption, satisfaction, safety)									X	X	
Socio-demographic questions (age, gender, ethnicity, prior occupation, country of origin, educational level, pet ownership, marital status, living arrangements, alcohol frequency smoking frequency, medication info, medical history)		X									
activPAL measurements (sitting time, sit-to-stand transitions, no. of sedentary bouts ≥ 30 mins, avg. length of sedentary bouts, stepping time, standing time, steps per day)		X							X	X	
International Physical Activity Questionnaire–Short Form (IPAQ-SF) [39]		X							X		
Measure of older adults’ sedentary behaviour (MOST) [40]		X							X	X	
Quality of life (QoL) (EuroQoL 5D-5L, EuroQoL Visual Analogue Scale) [41]		X							X	X	
Oxford Hip and Knee Score(s) [42, 43]		X							X	X	
Basic Psychological Needs Scale [25, 26]		X							X	X	
Activities of daily living (ADL) (Katz-ADL) [37]		X							X		
Physical function–Short Physical Performance Battery (SPPB) [36]		X							X	X	
Short Form Mini Nutritional Assessment (SF-MNA) [37]		X									
Weight		X							X	X	
Height		X									
Body mass index		X							X	X	
Waist-to-hip ratio		X							X		
Albumin, high-density lipoprotein, low-density lipoprotein, cholesterol, triglycerides, vitamin D, cortisol, transferrin, HBA1c, CRP, full blood count		X							X		

*R* researcher, *PC* phone call, *CRP* C-reactive protein

Due to the variation in surgery scheduling and the difficulty in obtaining accurate surgery dates months in advance, not all participants may undergo the same duration of intervention. The intervention is intended to be of 6-weeks’ duration but can be extended or shortened where required. Individuals will receive visit 4 in the week leading up to their surgery and will receive visit 5 6-weeks post-operatively. Most individuals are expected to have surgery 4–10 weeks after visit 3. Participants are expected to participate in the study for a total of 15–18 weeks. The variability in intervention delivery and timings will be recorded to help inform the assessment of study feasibility.

#### Usual care

The usual care group will undergo three study visits: baseline (visit 1), pre-surgery (visit 4), and post-surgery (visit 5). Otherwise, they will have regular orthopaedic care in line with other non-study patients, but will be contacted by telephone every 2 weeks to follow up about the status of their ongoing care. However, the calls will not be pre-planned and will not entail any BCTs.

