### Safety monitoring

All potentially serious adverse events, defined as any event that could be related to the study and that caused injury or hospitalisation, will be reported to the principal investigator and the study’s clinical orthopaedic consultant ([name]) within 24 h of the team being aware of its occurrence and will be reported to the sponsor within the same period. Additionally, any concerning blood results or evidence of risk of malnutrition will be reported to the principal investigator and the patient’s medical team.

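### Table 2 and the Usual care text disagree on whether control patients are telephoned, so falls and injuries could be detected unequally between arms, in a direction the article does not fix

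*Protocol article*

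**What the plan says.** **Usual care.** The Usual care section states that these patients "will be contacted by telephone every 2 weeks to follow up about the status of their ongoing care". It continues: "However, the calls will not be pre-planned and will not entail any BCTs". It names neither a first nor a last call.

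**Table 2.** The schedule has three phone call columns, at weeks 5, 7 and 9. All three are marked in the intervention row and all three are blank in the Regular care row. The accompanying text (Intervention structure and delivery) says: "The usual care group will attend only three visits, namely, 1, 4, and 5, which are assessment-only visits".

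**Intervention arm.** Under Intervention components, "three biweekly phone calls with the researcher will use motivational interviewing techniques"; they deal with progress on goals and are scheduled at visit 3. There are also extra visits: "The intervention group, however, will also attend visits 2 and 3 (which may be combined if time permits").

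**Safety.** Under Safety monitoring, potentially serious events are those possibly linked to the study that led to injury or a hospital stay. They must be reported within 24 h "of the team being aware of its occurrence". The Discussion says that data on hospital admissions and surgical complications could not be collected. The feasibility questionnaire, with one version per arm, includes safety and is marked at visits 4 and 5 in Table 2. The fifth progression criterion asks the study's medical expert whether adverse event frequency puts the trial's safety in doubt. Its rationale names falls from extra walking and standing.

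**The concern.** If reporting begins with awareness and hospital data are not available, the team learns of events largely through contact with the participant. The contact schedule is then part of the safety measurement. For the intervention arm that schedule is fixed. For usual care the article gives two schedules that differ, and the one in the text is open-ended and not planned ahead. The two sets of calls also have different stated purposes: goal progress in one arm, status of care in the other.

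What is at stake is the reading of adverse event frequency at progression. The article gives no background rate of falls or injuries in people awaiting hip or knee replacement, so the 15 usual care patients are the only reference inside the trial. If their events are sought less often, or more often, than those of the 30 intervention patients, a difference between arms mixes detection with any effect of the intervention.

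**Working it through.** The article states no figure to reproduce here. The check is a count of contacts per arm under each reading.

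**Inputs**
- Intervention calls: 3, at weeks 5, 7 and 9, with visit 3 at week 3 (Table 2). They therefore fall 2, 4 and 6 weeks after visit 3.
- Extra intervention visits: 2, or 1 if combined.
- Usual care calls: 0 by Table 2; one per 2 weeks by the text.
- Time from visit 3 to surgery, W: "Most individuals are expected to have surgery 4–10 weeks after visit 3". The intended intervention lasts 6 weeks.
- Visit 4 is 1 week before surgery and visit 5 is 6 weeks after it, so they are 1 + 6 = 7 weeks apart.

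**Reading 1: Table 2.** Intervention contacts between visits 1 and 4 = 3 calls + 1 to 2 visits = 4 to 5. Usual care contacts = 0.

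**Reading 2: the text.** Usual care calls = floor(W/2), counted from the week of visit 3 to surgery.

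| W (weeks) | Intervention calls | Usual care calls, Table 2 | Usual care calls, text |
|---|---|---|---|
| 4 | 3 (2 if kept to the Table 2 weeks) | 0 | 2 |
| 6 | 3 | 0 | 3 |
| 8 | 3 | 0 | 4 |
| 10 | 3 | 0 | 5 |

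Stopping the usual care count at visit 4 removes at most one call (3 at 8 weeks, 4 at 10 weeks). The article gives no start or end, so this one-call uncertainty cannot be resolved.

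Adding visits 2 and 3, total contacts under the text are 4–5 against 3 at 6 weeks, 4–5 against 4 at 8 weeks, and 4–5 against 5 at 10 weeks. Visits 2 and 3 both fall in week 3, one week after baseline and before goals are acted on, so they add little observation time for events during the intervention.

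**After visit 4.** If two-weekly calls run on to visit 5, usual care receives floor(7/2) = 3 further calls. The intervention arm has none scheduled.

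**Result.** By Table 2 the intervention arm is watched much more closely. By the text the arms are about level over the intended 6 weeks, and usual care is called more often when surgery is late and possibly after visit 4.

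**The case against.** **The conflict may be only apparent.** The phone call columns could show the intervention's own calls, and calls that are not pre-planned have no natural place in a grid of fixed weeks. This is a fair reading. Even so, the participant schedule then omits a recurring contact for one arm, and the end of those calls stays unstated.

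**One team runs the trial.** It is single-site, and 4–5 against 0 arises only if the researcher disregards an explicit sentence. This stands: that count is the extreme case, and roughly 3 against 3 is the more likely one.

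**Shared sources exist.** Both arms complete the questionnaire at visits 4 and 5, and the university's compliance team reviews adverse events. This narrows the gap, although the article does not say that the questionnaire records falls or injuries. Reportable events are also those causing injury or a hospital stay, which patients are less likely to forget than minor falls.

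**Stronger readings.** A reader might infer that events would certainly be detected unequally, or that the progression decision will go wrong as a result. The documents do not support either. Under the text, call frequency is about equal over 6 weeks. The fifth criterion is an overall expert judgement with no stated comparison of arms, and no formal between-group testing is planned. A reader might also want a biased rate ratio, but the article gives no recall rates and does not say that either arm's calls ask about falls, so any such ratio would be invented.

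**Call scripts belong in the full protocol.** Agreed: the lack of a script in the article is not the finding. The disagreement between text and table is.

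**Conclusion.** The point holds in a limited form. The Usual care section and Table 2 do not agree on telephone contact, and the text fixes neither the timing nor the end of the calls. Because event reporting depends on awareness and hospital data could not be collected, falls and injuries could be detected unequally. Both size and direction depend on which passage is followed: contacts of 4–5 against 0 before surgery under Table 2; calls of about 3 against 3 over 6 weeks and 3 against 4–5 at 8–10 weeks under the text.

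The counts assume that calls keep strictly to two weeks and start from the week of visit 3. That awareness comes mainly through contact with participants is an inference from the Safety monitoring and Discussion sections. The consequence is a weaker reference group for judging adverse event frequency, not a demonstrated bias in the progression decision. It merits a cheap correction.

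**What to change.** 1. Reconcile the two places. Show the usual care calls in Table 2 on the same two-weekly schedule as the intervention calls, and amend the Usual care text to match.
2. State until which visit calls run, identically in both arms. If that goes beyond the third intervention call, confine the later intervention calls to the event questions so that the intervention itself is unchanged.
3. Open every call, and visits 4 and 5, with the same short questions in both arms on falls, injuries and admissions, before any talk of goals.
4. Report all adverse events by arm with their source (call, visit, spontaneous report, other). Give events elicited at the common contacts per person-week as the comparable subset. Do not exclude spontaneously reported events.

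Recruitment was expected to end in January 2019. For patients already followed, the remedy is to report the calls actually made in each arm and the source of each event.

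**Cost.** One amended row in Table 2, one sentence on the end point and a short script. The usual care calls are already committed to. Carrying calls to surgery in the intervention arm would add up to 5 − 3 = 2 brief calls when surgery is 10 weeks after visit 3. The downside is slight extra attention to usual care.

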#### Intervention fidelity assessment

All goals and environmental modifications made during the study will be recorded and qualitatively coded after cessation of the study. Ratings of skill used in this study will utilise specifically-designed checklists based on the five-stage model of adult skill acquisition by Dreyfus et al., which has been used successfully in prior trials [32–34]. The fidelity tool is available in Additional file 3. Ratings of fidelity will be recorded digitally on forms specific to each intervention session and phone call and will be quantitatively analysed after cessation of the study.

Skills assessed will include motivational interviewing, problem-solving, progress monitoring, setback managing, and action planning. These will be assessed on a per-session basis where relevant. Action plans will also be reviewed for content, quality (adherence to SMART principles), and suitability for improving patient physical function. The researcher will self-rate a subset of action planning sessions for proper utilisation of all the relevant skills (e.g. whether patient autonomy was supported). A subset of the motivational interviews will be audio-recorded and checked for quality of delivery by an expert member of the study team (CG) using the same checklist. A further subset of the motivational interviews will be commented on by the researcher using field notes and subsequently qualitatively analysed. A subset of the phone calls will be immediately self-rated by the deliverer for the usage of motivational interviewing, problem solving, progress monitoring, and setback management skills.

### Study assessments

#### Primary outcome assessment

##### Feasibility (study statistics)

Feasibility will be assessed primarily using the following study statistics:Study uptake rate—percentage of participants whom receive a PIS who subsequently enrol in the study (%).Recruitment rates—average number of participants recruited per month.Intervention adherence—average self-reported goal adherence (scale 1–5) per week (recorded in sedentary behaviour booklet).Percentage of participants whose surgery occurs eight or more weeks after visit 3 (%).Percentage of participants whose surgery is scheduled four or fewer weeks after visit 3 (%).Percentage of participants with indefinitely delayed or cancelled surgery—proportion of participants who will not have surgery within the lifetime of the study (%).Retention rates—percentage of participants who remain in the study (i.e. provide measures) and do not drop-out at each follow-up timepoint (%).Average duration of intervention—average number of weeks of participation in the intervention prior to surgery.Session attendance—number of intervention sessions attended and the associated total contact time.

#### Secondary outcome assessment

##### Feasibility questionnaire

Feasibility will be assessed secondarily by the use of bespoke questionnaires that comprise both open and closed questions: one for the usual care and one for the intervention group. Each question is designed to target an aspect of feasibility based on guidance by Bowen et al. [35]. The questionnaires assess acceptability, practicality, adaption, satisfaction/feedback, and safety/risk for the participant. These files are available as Additional files 4 (usual care) and 5 (intervention).

##### Qualitative interviews with healthcare staff

One semi-structured qualitative interview will be conducted after the cessation of recruitment with each research nurse who had a significant role in recruitment for the study. These will assess how feasible the recruitment process was from their perspective and provide valuable insight into whether improvements could be made to recruitment and study processes in a future definitive trial. A topic guide is available in Additional file 6.

#### Sociodemographic information

Data will be collected regarding participant age, gender, country of origin, language used at home, marital status, ethnicity, educational qualifications, years of school, main occupation, living arrangements, housing, pet ownership, alcohol drinking status and frequency, smoking status and frequency, and former smoking and drinking behaviour. Data regarding current medications and medical conditions will also be collected.

#### Exploratory outcomes

To assess the feasibility of collecting data to inform the efficacy of the intervention in this population, the following measures will be performed:Physiological measurements: weight (kg), height (cm), body mass index (kg/m^2^), hip circumference (cm), waist circumference (cm), and waist-to-hip ratio (cm).Objective assessment of sedentary behaviour and physical activity using activPAL3 inclinometers: daily sitting time, mean daily sit-to-stand transitions, daily number of sedentary bouts ≥ 30 mins, avg. length of sedentary bouts, stepping time (mean per day), standing time (mean per day), and mean steps per day.Physical function: The Short Physical Performance Battery will be used. This gives a score of 0–12 across the domains of balance (4 points), 4-m walk test (4 points), and time to perform 5 chair rises without using the arms (4 points) [36].Activities of daily living: Katz Activities of Daily Living Scale (0–6 score), based on a score for how independent participants are in bathing, dressing, toileting, transferring from bed to chair, continence, and feeding [37].Nutritional status: Short Form Mini Nutritional Assessment, assesses the risk of malnutrition (score 0–14) [38].Subjective assessment of physical activity: International Physical Activity Questionnaire (Short Form) [39]. Provides self-reported data regarding minutes of vigorous physical activity (h/week), moderate physical activity (h/week), walking (h/week), and sitting (h/day).Subjective assessment of sitting: Measure of Older Adults’ Sedentary Behaviour [40]. Assesses self-reported sitting hours per week in multiple behaviours: watching television/video, time on computer/internet, reading, socialising with friends/family, driving or riding in a vehicle, hobbies, and other activities (will be reported in total hours/day, and hours/week for each sub-domain).Quality of life: EuroQol 5D-5L and EuroQoL Visual Analogue Scale [41]. The former consists of 1–5 scores across domains of mobility, self-care, usual activities, pain/discomfort, and anxiety/depression, and the latter consists of a 0–100 self-rating of overall health. The former will be reported for each sub-domain.Impact of osteoarthritis: Oxford Knee Score and Oxford Hip Score [42, 43]. This provides a score from 0 to 48 across 12 questions with 5 options each, where a score of 0 is the most severe. The scale covers pain, impact on daily activities, and more. Overall score will be reported.Basic psychological needs: Basic Psychological Needs Scale in General [23, 25]. This provides a score for autonomy, competence, and relatedness across 21 questions (7 each). Scores of 0–7 are output for each need.Blood test–cardiometabolic biomarkers: albumin (g/L), high-density lipoprotein (mmol/L), low-density lipoprotein (mmol/L), cholesterol (mmol/L), triglycerides (mmol/L), vitamin D (ng/mL), cortisol (nmol/L), transferrin (g/L), HBA1c (nmol/mol), and C-reactive protein (mg/L). Blood will be collected via venepuncture at the site of the visit by a trained phlebotomist and taken immediately post-visitation for analysis at the University Hospitals Birmingham Clinical Laboratory Services. This blood is not stored.

The measurement timepoints are listed in Table 2, and the rationale for these measures can be read in Additional file 7. These data will inform the design of a definitive trial by helping to identify which outcomes are feasible, which demonstrate the greatest responsiveness to the intervention, and what sample size is needed to provide sufficient statistical power to detect changes in the primary outcome (calculated from standard deviations for changes in the outcome measures). Data will be retained and analysed on an intention-to-treat basis.

